#### Hypothesis two: physician judgments of the likelihood of treatment outcomes will sometimes be inaccurate

To evaluate this hypothesis, data from the Type 1 surveys will be used to test whether judged outcome likelihoods for a representative patient match best evidence from systematic reviews. For example, judged absolute increase in resolution of symptoms due to antibiotics use will be computed as described above (hypothesis one). This will allow the comparison of judged estimates with the 95% confidence intervals reported by these trials and tabulation of the percentage of physicians that are outside the 95% confidence intervals (i.e. maintaining beliefs that have been "ruled out" by the trials). We will display the distribution of the physicians' judgments compared to the trials' best estimate and surrounding 95% confidence intervals.

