## Abstract

**Background:**

There are many examples of physicians using treatments inappropriately, despite clear evidence about the circumstances under which the benefits of such treatments outweigh their harms. When such over- or under- use of treatments occurs for common diseases, the burden to the healthcare system and risks to patients can be substantial. We propose that a major contributor to inappropriate treatment may be how clinicians judge the likelihood of important treatment outcomes, and how these judgments influence their treatment decisions. The current study will examine the role of judged outcome probabilities and other cognitive factors in the context of two clinical treatment decisions: 1) prescription of antibiotics for sore throat, where we hypothesize overestimation of benefit and underestimation of harm leads to over-prescription of antibiotics; and 2) initiation of anticoagulation for patients with atrial fibrillation (AF), where we hypothesize that underestimation of benefit and overestimation of harm leads to under-prescription of warfarin.

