**Discussion:**

This work will provide insight into the extent to which clinicians' judgments about the likelihood of important treatment outcomes explain inappropriate treatment decisions. This work will also provide information necessary for the development of an individualized feedback tool designed to improve treatment decisions. The techniques developed here have the potential to be applicable to a wide range of clinical areas where inappropriate utilization stems from biased judgments.

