### Examples of clinical therapies that are inappropriately utilized

This project will examine whether inappropriate treatment decisions are associated with judged outcome probabilities and judgment biases. Two clinical conditions were selected; one in which treatment is generally over-utilized, the other where it is under-utilized. We examine both over- and under-utilization because changing an existing, well-practiced behaviour (i.e. reducing the use of over-utilized treatments) may require different change mechanisms than beginning a new behaviour (i.e. adopting an under-utilized treatment). This proposal focuses on two specific treatments: the over-prescription of antibiotics for pharyngitis treatment, and the under-use of warfarin (Coumadin) for treatment of chronic AF.

Our goal for both clinical conditions is to understand relationships between treatment decisions and judged probabilities of 'outcomes'; i.e. the benefits and harms that might stem from a given treatment. In the case of warfarin treatment for AF, key outcomes will include stroke (fatal or permanently disabling) and major hemorrhages (fatal, intracranial, or other bleeds requiring hospitalization). In the case of antibiotics for pharyngitis, relevant outcomes include resolution of symptoms, local and systemic complications from such infections (e.g., perotonsillar abscess and glomerulonephritis), and complications of treatment, such as adverse drug reactions (ADRs).

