### Hypotheses

We will examine the role of judged outcome probabilities and judgment biases for two kinds of treatment decisions: use of antibiotics for patients with pharyngitis, and use of anti-coagulants for treatment of AF. The study will address five specific hypotheses:

1. Physicians' decisions to use specific treatments depend on their judgments of the likelihood of treatment outcomes.

2. Physician judgments of the likelihood of treatment outcomes will sometimes be inaccurate;

3. Specific judgment heuristics can account for some of the inaccuracies of physician judgments of treatment outcomes;

4. Predictable groups of physicians will be more apt to be inaccurate in their judgments of treatment outcomes;

5. Judgment inaccuracies will stem from physicians attending to cues that are unrelated to treatment outcomes, and/or insufficiently attending to cues that are related to outcomes.

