### Procedure

The primary goals of the Type 1 surveys will be to assess physicians' perceived outcome probabilities (good and bad) for different treatments, and to compare these perceived probabilities to the real rates indicated by systematic reviews (hypothesis two). These goals will be achieved by having physicians assess a hypothetical patient representative of those included in the most important and relevant RCTs of the target condition. The survey will assess judged outcome probabilities, by asking physicians to quantify the likelihood of various outcomes if a hundred patients similar to this hypothetical patient were to be treated. The Type 1 surveys will also ask physicians about how they currently treat such cases, the recollection of rare or vivid outcomes (hypothesis three), as well as practice and demographic details.

The primary goals of the Type 2 surveys will be to measure specific factors that drive individual clinician judgments and treatment decisions (hypothesis five), and to determine whether individual physician judgments predict treatment decisions (hypothesis one). These goals will be achieved by having physicians consider sixteen realistic case vignettes about hypothetical patients with the target condition. Eight clinical variables will be varied systematically across the sixteen case vignettes using a partial factorial design. For example, the manipulated variables in the antibiotics vignettes could include factors related to clinical outcomes (e.g. Centor criteria predicting strep: cough, fever, tonsillar exudates, tender lymph nodes), as well as non-predictive variables that might be perceived as predictive (e.g. age, sex, occupation). The vignettes will prompt physicians to indicate what management decision they would select for each clinical variable combination. These responses will allow for the identification of which variables have the greatest effect on physician judgments, and whether such judgments are affected by non-predictive cues or the unrealistic expectations of appropriate cues.

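### The abstract states the direction in which judgments err, but the only percentage tabulated for hypothesis two pools both directions, and no described analysis relates Type 1 judgments to Type 1 stated treatment

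*Protocol article*

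**What the plan says.** The Background paragraph of the abstract gives one directional claim per condition. For antibiotics: "we hypothesize overestimation of benefit and underestimation of harm leads to over-prescription of antibiotics". For warfarin: "we hypothesize that underestimation of benefit and overestimation of harm leads to under-prescription of warfarin". The section on inappropriately utilized therapies sets a related aim without a direction: "This project will examine whether inappropriate treatment decisions are associated with judged outcome probabilities and judgment biases".

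The formal list under Hypotheses drops the direction. Hypothesis two reads: "Physician judgments of the likelihood of treatment outcomes will sometimes be inaccurate". Its analysis section plans "tabulation of the percentage of physicians that are outside the 95% confidence intervals", plus a display of the distribution of judgments against the trials' best estimate and interval. Judged benefit is to be computed as under hypothesis one.

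Under Procedure, the Type 1 surveys are meant "to assess physicians' perceived outcome probabilities (good and bad) for different treatments, and to compare these perceived probabilities to the real rates". The same section adds: "The Type 1 surveys will also ask physicians about how they currently treat such cases". The four surveys go to different random samples, so the Type 1 and Type 2 respondents are different physicians.

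**The concern.** A percentage outside the interval measures how often physicians are wrong, not which way. Scatter on both sides and a systematic bias can produce the same figure, yet only systematic bias in the stated direction fits the abstract's claim.

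The abstract also says that the error leads to the prescribing pattern. Type 1 is the only survey in which the same physician supplies both a judgment compared with trial evidence and a stated current treatment, and none of the described analyses brings the two together.

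The abstract's Discussion paragraph says the work will show how far "judgments about the likelihood of important treatment outcomes explain inappropriate treatment decisions", and the results are to inform a feedback tool. Designers of that tool would need to know which way judgments err, and whether physicians who err that way are the ones who treat accordingly.

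**Working it through.** **1. The plan's own precision figure.** From Sample size and power: 300 mailed × 0.94 eligible × 0.50 responding = 141. Half-width for the hypothesis two percentage at p = 0.5: 1.96 × √(0.25/141) = 0.0825, against the stated 0.082. It reproduces, and it describes the pooled percentage.

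**2. What the pooled percentage cannot distinguish.** Assume 60% of 141 fall outside the interval. Let d = proportion above − proportion below, with variance (above + below − d²)/141.

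| Above | Below | Tabulated as outside | d ± 1.96 SE |
|---|---|---|---|
| 60% | 0% | 60% | +0.60 ± 1.96√(0.24/141) = +0.60 ± 0.08 |
| 30% | 30% | 60% | 0.00 ± 1.96√(0.60/141) = 0.00 ± 0.13 |
| 0% | 60% | 60% | −0.60 ± 0.08 |

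Only the first row fits the claim for antibiotic benefit. Each one-sided percentage would also have a half-width of at most 0.0825, so splitting the figure costs no precision against the plan's own bound.

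**3. What the five analyses relate.**

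| Hypothesis | Survey | Response | Explained by |
|---|---|---|---|
| One | Type 2 | Treatment decision | Judged likelihood, not compared with evidence |
| Two | Type 1 | Percentage outside the interval | Nothing; descriptive |
| Three | Type 1 | Judged likelihood | Recalled rare outcomes, physician characteristics |
| Four | Type 1, warfarin | Accuracy | Specialty, with covariates |
| Five | Type 2 | Judged probability | Vignette cues |

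None has Type 1 stated treatment as the response. The nearest item in the covariate list, current test ordering practice, is a covariate and concerns testing.

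**4. The sign of judged benefit.** Hypothesis one asks for (1) the proportion resolving with no antibiotic, P₀, and (2) the proportion resolving with penicillin, P₁. It takes the second from the first, P₀ − P₁, and calls the result an absolute increase due to the antibiotic. If the antibiotic is judged to help, P₁ > P₀ and the result is negative; the increase is P₁ − P₀. Hypothesis two reuses this computation. If the trial effect is expressed as an increase, the sides of the interval would be misassigned.

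**5. Does scoring against evidence change the slope?** Type 1 uses one representative patient, so the benchmark c is a constant. In logit(p) = a + b(J − c) = (a − bc) + bJ, the slope b is the same for signed error (J − c) and raw judgment J. Only the intercept moves.

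**6. What a Type 1 regression could detect.** Two-sided 5%, 80% power, one standardised predictor, no adjustment: OR per SD = exp(2.80/√(n·p(1−p))), where p is the assumed share who would treat.

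| n | p = 0.5 | p = 0.6 | p = 0.7 |
|---|---|---|---|
| 141 (antibiotics) | 1.60 | 1.62 | 1.67 |
| 282 (warfarin, both specialties) | 1.40 | 1.41 | 1.44 |

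If other terms explained 30% of the predictor's variance (an assumption), the exponent is divided by √0.7, and the range at n = 141 becomes 1.76 (p = 0.5) to 1.85 (p = 0.7).

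**7. Covariate load.** The plan counts 8 df and requires 15 observations per df (120). Judged benefit and judged harm add 2, giving 10 × 15 = 150, which exceeds 141 but not 282. At n = 141 with 50–70% treating, the rarer response has about 42 to 71 physicians, or 4 to 7 per df.

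**The case against.** A reader might infer that the directional claim goes wholly untested. The documents do not support that. The claim has two links. Hypothesis one tests the second, from judgment to decision, with a coefficient that carries a sign, sixteen vignettes per physician and physician-specific slopes. For the first link, the planned display would let anyone see an even split or a one-sided shift.

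It is also no defect of hypothesis one that its judgments are not compared with evidence. As step 5 shows, for a single representative patient that comparison would leave the slope unchanged.

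The pooled percentage suits hypothesis two as listed, which has no direction: a belief excluded by the trials counts on either side. The directional sentences are in the abstract, not among the five hypotheses. A condensed article may also leave tabulation detail to a fuller plan, and nothing in it forbids reporting by side.

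Most of this stands, and it limits the point. What remains is that the article names one summary figure and states precision for it, and that figure cannot answer the abstract's claim. A plot gives no estimate of direction and no interval. Hypotheses one and two together do not supply the missing link either: judgments can drive decisions and many can be inaccurate without the overestimators being the prescribers, and the two surveys reach different physicians.

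**Conclusion.** The point holds as a mismatch between the abstract's claim and the summary planned for hypothesis two, and as an unused opportunity in Type 1. No sample size or precision figure checked here is wrong. The one error of fact is the reversed subtraction, which matters as soon as results are reported by direction.

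The size depends on how errors divide: the same 60% could mean a net direction anywhere from −0.60 to +0.60. The 60% is illustrative; the documents give no expected value.

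The detectable odds ratios rest on an assumed 50–70% of physicians treating. The article's 57–74% is a share of patients, not physicians, and does not settle this. The values are unadjusted and for a single predictor, so those for the antibiotic survey are optimistic.

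It would also go too far to infer that the Type 1 regression would establish that misjudgment leads to inappropriate prescribing. It is cross-sectional, and physicians may form estimates that justify existing habits. It can support the association named in the aim and no more. The article itself leaves the question of whether better judgments change treatment to a later randomised trial.

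**What to change.** 1. **Correct the subtraction** under hypothesis one, so that judged benefit is the proportion resolving with penicillin minus the proportion resolving without an antibiotic, and carry this into hypothesis two. Fix a sign convention for each outcome, so that a positive error always means more benefit, or more harm, than the evidence shows.
2. **Report hypothesis two by side.** For each benefit and harm outcome, give the percentage above the upper limit and the percentage below the lower limit, each with its confidence interval, and the median signed error with its confidence interval. State the expected signs in advance: for antibiotics, positive for benefit and negative for harm; for warfarin, the reverse. Keep the pooled percentage and the display.
3. **Add one exploratory Type 1 analysis per condition.** Regress stated current treatment of the representative patient on judged benefit and judged harm. In the antibiotic survey keep the covariate set small enough to meet the plan's own rule: 141/15 = 9.4, so at most 9 df in all, of which the two judgments take 2. The warfarin survey, with 282 expected, can carry the full list. Describe the result as association.

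The cost is analysis wording and a few table rows. Items 1 and 2 need no new survey item, model or respondents. Item 3 uses a question already planned for the Type 1 surveys.

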#### Hypothesis three: specific judgment heuristics can account for some of the inaccuracies of physician judgments of treatment outcomes

Type 1 surveys will include questions on whether rare or vivid outcomes had been seen by the physician in the previous year. The extent to which the answers to this question affect judgment accuracy will be analyzed using an approach similar to that for hypothesis one. Note, however, that there will only be one observation per physician, therefore hierarchical modeling will not be required. This analysis will test whether experience of and memory for rare, bizarre, or vivid outcomes (e.g. suppurative complication of a streptococcal infection) affect the assessment of the overall likelihood of such an outcome. The response variable in the regression models will be the assessment of the likelihood of outcome for the case presented in the Type 1 survey. Independent variables will include physician characteristics (e.g. demographics, specialty, and practice setting) and the physicians' recollections of rare outcomes.

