## Methods

Four surveys will be mailed to Canadian physicians, two focused on the use of antibiotics for pharyngitis, and two on the use of anti-coagulants for treatment of AF. For each clinical condition, one survey (Type 1) will measure the accuracy of judged probabilities of treatment-related outcomes, while the other (Type 2) will use a series of realistic case vignettes to determine what factors affect treatment decisions.

Development of the various surveys will require us to perform the following tasks: systematically review the relevant clinical literatures to identify the characteristics of patients to whom the research results would generalize; identify the important outcomes, good and bad, conditional on treatment; develop evidence-based estimates of the population rates of these outcomes conditional on choice of treatment; and assess the evidence about patient factors that may predict these outcomes. We will also review the available evidence about factors that influence physicians' decisions around use of the treatment. We will construct and pilot test surveys to evaluate physicians' judgments and decisions based on this work. These surveys will be informed by pilot work done in the US on a different range of clinical subspecialties.

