#### Hypothesis five: some judgment inaccuracies will stem from physicians overweighting cues that are unrelated to treatment outcomes, and/or underweighting cues that are related to outcomes

This hypothesis will be evaluated using data from the Type 2 surveys. The analytical approach is identical to that described in hypothesis one, with the response variable being "judged probability" instead of treatment decision. This approach is conceptually inspired by lens modeling, otherwise known as social judgment analysis [85-87]. The approach involves systematically varying the levels of several sources of information (cues) between a series of vignettes. From these vignettes, the judgment strategies employed by physicians when making their diagnoses can be inferred. This judgment strategy can be represented as a linear regression model, with standardized regression weights describing the relative importance of each cue in determining a physician's diagnosis. While the linear model does not necessarily indicate what the physician was thinking at the time of judgment, it will predict those judgments accurately [88], and indicate which cues affected judgment [89].

We will also tabulate the proportion of physicians for whom one or more of the non-predictive variables have coefficients different from zero, as assessed by the 95% posterior probability region; this implies these variables are used as predictors of either benefits or harms. We will then tabulate the proportion of physicians using each specific type of variable to make their judgments.

For all regression models, we will employ graphical approaches to look for outliers and influential observations, while statistics measuring model fit will also be calculated. Steps to control the extent of missing data items will be built into each aspect of the data collection and data management process. During the final analysis of the data we will rely on multiple imputation techniques to handle the presence of missing data elements. We will also compare the results to those obtained from the analysis based on complete cases only.

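### Hypothesis three announces accuracy but models the raw judgment, and hypothesis five has no reference weight for predictive cues, so size of error and partial underweighting are not tested

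*Protocol article*

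**What the plan says.** **Hypothesis three.** The heading of this Analysis subsection claims that "specific judgment heuristics can account for some of the inaccuracies of physician judgments of treatment outcomes". The text announces that "The extent to which the answers to this question affect judgment accuracy will be analyzed", and then defines the outcome differently: "The response variable in the regression models will be the assessment of the likelihood of outcome". The predictors are physician characteristics and recollection of rare outcomes. The design is one case per respondent: "there will only be one observation per physician, therefore hierarchical modeling will not be required". No best-evidence value enters the model. Hypothesis four, by contrast, does compare judgments with best evidence before comparing groups.

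**Hypothesis five.** The subsection heading covers two arms: overweighting of unrelated cues, and "underweighting cues that are related to outcomes". The analysis repeats that of hypothesis one with judged probability as the response, and describes cue importance by standardised weights. The one stated criterion is whether coefficients of non-predictive variables differ from zero by a 95% posterior region. A tabulation of which types of variable physicians use follows. The Methods section plans, as a survey-development task, to "assess the evidence about patient factors that may predict these outcomes", but the hypothesis-five analysis does not take this up.

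**The concern.** A higher judged likelihood is not the same as a worse one. The Abstract expects harm to be underestimated for antibiotics and overestimated for warfarin. Suppose that recalling a side effect raises judged harm in both surveys. The same positive slope would then go with smaller error for antibiotics (unless recallers overshoot by as much as the others undershoot) and with larger error for warfarin. The model as written cannot tell these apart.

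For hypothesis five, zero is the correct reference for a cue that does not predict the outcome. For a cue that does, underweighting means a weight smaller than the evidence supports, and a coefficient alone cannot show that.

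The Discussion relies on this study to identify sources of inaccuracy and to choose feedback for the next phase. Recall that brings judgments closer to the evidence could be treated as a bias to correct, and underused predictive cues could go unnoticed.

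**Working it through.** **Plan figures reproduced (Sample size and power).** Covariate df: 1 + 2 + 2 + 1 + 1 + 1 = 8, and 8 × 15 = 120 respondents needed. Expected: 300 × 0.94 = 282, and 282 × 0.50 = 141. Both agree with the plan. The point below concerns the response variable and changes neither figure.

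**Hypothesis three, algebra.** Let Y be the judged likelihood, x the recall indicator and T the best-evidence value for that outcome. T is one constant because all respondents to a survey judge the same case.
- Planned model: Y = b0 + b1·x + e.
- Signed error: Y − T = (b0 − T) + b1·x + e. The slope is the same b1; only the intercept moves.
- Absolute error |Y − T|: its slope depends on where T lies and cannot be read from b1.

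**Hypothesis three, illustration.** The documents give no benchmark or effect, so these inputs are assumptions: non-recallers average 5 per 100, recall adds 2, SD 2, 30% recall, n = 141, 2,000 simulated surveys, least squares.

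| Assumed T (per 100) | Slope, raw judgment | Slope, signed error | Slope, absolute error |
|---|---|---|---|
| 2 | 1.99 | 1.99 | +1.88 |
| 6 | 2.01 | 2.01 | +0.01 |
| 10 | 2.00 | 2.00 | −1.89 |

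Raw and signed slopes agreed in every run to within rounding error (below 1e-14). The group averages show why the last column changes sign:
- T = 2: |7 − 2| − |5 − 2| = 5 − 3 = +2.
- T = 6: |7 − 6| − |5 − 6| = 1 − 1 = 0.
- T = 10: |7 − 10| − |5 − 10| = 3 − 5 = −2.

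**Hypothesis five, algebra.** Let b be the judged weight of a cue and w the weight that the evidence supports, both in points per 100, with effects taken as additive. Regressing (judged − evidence) on the cues gives b − w.
- Unrelated cue, w = 0: b − w = b, so a test of b against zero is a test of overweighting.
- Predictive cue, with b = 10 as an assumed value: w = 5 gives +5 (overweighted), w = 10 gives 0 (correct), w = 20 gives −10 (underweighted by half). The planned regression returns 10 in all three cases.

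Standardised weights do not help, because they rank cues within a physician and are not in points per 100. A coefficient near zero for a predictive cue can suggest neglect, but only as apparent non-use: sixteen vignettes with eight cues and an intercept leave 16 − 9 = 7 residual df per physician if each is fitted alone.

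**The case against.** A reader might infer that neither analysis can say anything about inaccuracy. The documents do not support that.
- With one case per survey, the raw slope already is the signed-error slope. Hypothesis two sets judgments from the same Type 1 data against the trial estimate and its interval, so the direction of error can be recovered by reading the two together.
- The unrelated-cue arm of hypothesis five is testable as planned, and complete neglect of a predictive cue could also show in the coefficients.
- The posterior-region rule is stated for non-predictive variables only. That a physician who underweights a predictive cue would simply be counted as using it is an inference, not something the plan says.

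A reader might also infer that hypothesis three could be declared supported by data showing the opposite. That goes too far. The Background defines availability by ease of recall, so a pattern in which physicians with nothing to recall underestimate most is compatible with the heuristic accounting for some error. For the same reason, requiring that recall increase absolute error would be too strict. It would reject a real recall effect of +2 in the T = 6 and T = 10 rows above. If the best estimate is close to zero, there is also little room to underestimate, and the raw and absolute-error slopes nearly coincide.

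Finally, a condensed article may leave details to a fuller plan. That answers part of the hypothesis-five point. It does not answer hypothesis three, where the response is stated and is not the quantity announced. Nor does it remove the underweighting claim attached to an analysis that, as described, contains no reference weight.

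**Conclusion.** The point holds in a limited form. The hypothesis-three text is inconsistent: it announces accuracy and models likelihood. Its slope shows whether recall shifts judgments, and equally whether it shifts signed error, but not whether recall goes with larger or smaller error. In the illustration the absolute-error slope ranges from +1.88 to −1.89 for the same recall effect of about +2.0. The sign reversal follows from the algebra; its size rests on the assumed benchmark, effect and spread. For hypothesis five, overweighting of unrelated cues is identified, while partial underweighting of predictive cues is not.

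The word causal does not belong in either the criticism or the remedy. Exposure is self-reported and unassigned ("Type 1 surveys will include questions on whether rare or vivid outcomes had been seen by the physician in the previous year"), so a different response variable would still give an association only.

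Two of five hypotheses are affected, one of them in one arm. Data collection and sample size are not.

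**What to change.** **Hypothesis three.** Keep the current model as the test of whether recall shifts judgments. Add deviation from the hypothesis-two best estimate as a response: signed and absolute, or an indicator of lying outside the 95% confidence interval. Draw conclusions about inaccuracy from the two models together, worded as association, and align the announced target with the stated response. The benchmark should come from the evidence-based outcome rates that the Methods section already plans.

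**Hypothesis five.** Where the planned review supplies a weight for a predictive cue, fix that weight before the data are seen. Compare the unstandardised judged coefficient, in points per 100, with it, and give a sensitivity range for the weight. Where the review supplies none, limit the conclusion to use of non-predictive cues and apparent non-use of predictive ones.

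**Cost.** Analysis wording, a few additional models on data already planned, and a short table of reference weights. The weights will be uncertain and may exist for only some cues, which is why the fallback wording is needed. Weights cue by cue are enough; a joint evidence-based likelihood for all sixteen vignettes is not required.
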